### Intervention

The stepped care intervention consists of four steps: *(1) Watchful waiting*. Patients with mood and anxiety disorders often recover spontaneously over time [34]. In the first step the patients receive no treatment for four weeks. In this project, only patients who still show symptoms of anxiety/depression after the watchful waiting period, are included. They start with (2) *Guided self-help*. Guided self-help starts with one 30 minute session with a care manager. This session enables the care manager to check exclusion criteria (e.g., severe psychopathology), to give psychoeducation (e.g., advice on lifestyle) and to explain the self-help interventions. In this study we have two different self-help interventions available. The first is a generic intervention based on problem solving treatment, which aims at patients with symptoms of mood and/or anxiety disorders. The Dutch version of self-examination therapy is called "*Alles onder controle*" and is available as a book and through the Internet. The patient can choose to get feedback by email or by telephone. In this study feedback is provided by coaches (members from the research group) from the VU University. The focus of the feedback is to guide the patient through the intervention by motivating and activating them. When patients send their assignments to their coach, they receive feedback within 3 working days. The second self-help intervention is specifically aimed at patients with phobias and is based on exposure therapy. In this course patients first have to make a list of all the situations that provoke anxiety and put them in order of intensity. Next they have to make a plan to practice exposure to these situations based on this anxiety hierarchy. This course takes six weeks to complete and is only available as a book. Feedback is therefore provided by telephone. During the first session, the care manager and the patient together decide which self-help course is most suitable. Patients who do not recover using self-help treatment start with (3) *Problem Solving Treatment (PST)*. PST is a short psychological intervention, 5 sessions of 45 minutes each, provided by the care manager [35]. The treatment protocol is based on '*Problem-solving treatment for anxiety and depression: A practical Guide*' by Laurence Mynors-Wallis [36]. Recent studies show that PST is an effective treatment for major depression as well as for more general, emotional disorders containing depressive and anxiety symptoms [35,37-42]. Training in PST was given by a problem solving treatment expert in a two-day course followed by weekly group supervision sessions. Patients who are unresponsive to this treatment will proceed to the last step of the stepped care program (4) *Pharmacotherapy and/or specialized mental health care*. In case patients do not recover from PST they have one more session with the care manager to discuss the next step: either pharmacotherapy or more specialized mental health care. In case a patient chooses pharmacotherapy, the care manager sets up an appointment for the patient with the GP. In case the patient chooses specialized mental health care, the care manager sets up an appointment with a mental health care specialist.

#### Exceptions

Even though there is no clear evidence that patients with more severe symptoms of anxiety or depression do not benefit from low intensity (self-help) interventions, we decided that patients with more severe disorders should be referred to more specialized mental health care and/or pharmacotherapy directly and skip the preceding steps. Severity of the disorders is based on questions about daily functioning on the Work and Social Adjustment Scale (WSAS) [43]. If the patient experiences extreme dysfunctioning (score of 8 or higher) on minimal three of the four domains (household, work, social relations and social activities) he will be directed immediately to the fourth step of the stepped care program.

#### Care as Usual

Patients randomised to the 'care as usual' will be informed about this outcome. They are informed that they can choose to find (mental) health care and are allowed to discuss this with their GP.

#### Assessments and definition of recovery

After each step in the stepped care intervention, patients are monitored: after 8 weeks (T1), 16 weeks (T2) and 24 weeks (T3). During each assessment we measure depressive symptoms, symptoms of anxiety and daily functioning. Recovery is defined as a score below the cut-off score on all three of the following questionnaires: having a score of less than 14 on the Inventory of Depressive Symptomatology (IDS) [44], a score of less than 8 on the Hospital Anxiety and Depression Scale [31] and a score of less than 6 on the WSAS [43]. This definition of recovery is based on several studies [44-48]. On account of the outcome of the monitor, we decide whether the patient is recovered or is 'stepping up' to the next step in the stepped care model.

##### Composite International Diagnostic Interview (CIDI)

The CIDI (version 2.1), a structured interview developed by the World Health Organisation [33], enables trained interviewers to assess psychiatric diagnosis defined in the Diagnostic and Statistical Manual of the American Psychiatric Association, 4^th ^edition [53]. The assessment typically lasts 30–75 minutes, depending on the mental state of the respondents [54]. In this study, current mental statuses within the last two months will be considered.

#### Primary outcome

##### Depressive symptoms

We will use the Inventory of Depressive Symptomatology (IDS) to measure depressive symptoms. The IDS consists of 26 items and the total score varies between 0 and 79. Scores below 14 indicate absence of depressive symptoms. We use this cut-off score as an indication of recovery from depressive symptoms [44,46]. Internal consistency is high for the IDS with Cronbach's alpha being .92 [44].

##### Anxiety symptoms

For identifying anxiety disorders we will use the Hospital Anxiety and Depression Scale (HADS) [31], which is usually used to identify anxiety disorders among patients in non psychiatric settings. The HADS consists of 7 items. Item responses are on a 0 to 4 scale (0="none" and higher ratings reflect greater degrees of symptom severity). Total-scores range from 0 to 21. The HADS showed good homogeneity and reliability, with Cronbach's alpha ranging from .81 to .84 in different normal and clinical Dutch samples [55].

##### Dysfunctioning

We will measure daily functioning of the patient via four questions of the Work and Social Adjustment Scale (WSAS) [43,56]. The patient gives an estimate, on a scale from 1 to 10, of the perceived dysfunctioning in daily live. The questions contain four domains: household, work, social relations and social activities.

#### Secondary outcome

##### Quality of life

Quality of life is measured through the MOS Short-Form general health survey (SF-20) which identifies the health related quality of life [57]. This self-report questionnaire (20 items) consists of six scales covering mental health, perceived health (mental and physical), social and role functioning, physical functioning and pain. A high score on the SF-20 indicates a high level of functioning, except for the subscale physical pain where a higher score indicates a higher level of pain. The alpha of the scales varies between .80 and .91 [57,58]. Quality of life is furthermore assessed using the EuroQol Questionnaire (EQ5D) [59], which is a validated tool for measuring general health related quality of life. It consists of five items (mobility, self-care, usual activities, pain/discomfort and anxiety/depression), each of which is rated as causing 'no problems', 'some problems' or 'extreme problems'. The EQ5D distinguishes 486 unique health states. Each unique health state has a utility score which ranges from 0 (poor health) to 1 (perfect health). EuroQol also contains a Visual Analogue Scale (VAS) on which patients rate their own health between 0 (worst imaginable health state) and 100 (best imaginable health state). Recently, a study in The Netherlands measured and valuated the EQ-5D in a national setting, resulting in the 'Dutch EQ-5D tariff' [60]. This tariff is used to calculate utilities for EQ-5D health states for cost-utility analyses of Dutch health care programmes and treatments.

##### Symptoms

The Four Dimensional Symptom Questionnaire (4DSQ) is developed for GPs to distinguish depression, anxiety and somatisation from more general distress [61]. The distress scale exists of 16 items and scores range from 0 – 32, the depression scale exists of 6 items and scores range from 0 – 12, the anxiety scale exists of 12 items and scores range from 0 – 24 and the somatisation scale exists of 16 items where scores range from 0 – 31. A higher score on the symptomatology indicates more serious complaints. The 4DSQ is a valid self-report questionnaire [61].

##### Alcohol use

The Alcohol Use Disorder Identification Test (AUDIT) [32] is a list of 10 questions about alcohol use. This test measures three different domains: quantity and frequency of alcohol use, the symptoms of alcohol dependency and the negative reactions on/consequences of alcohol use [62]. The score ranges from 0 – 40. A score of 9 or higher indicates a risk of an alcohol problem and a score of 13 and higher indicates the presence of an alcohol problem [63]. A study of Maisto et al. [62] shows that the AUDIT is a reliable and valid instrument. A score of 20 or higher on the AUDIT means exclusion from this study. Indices of internal consistency, including Cronbach's alpha and item total correlations, are generally in the .80's [64].

##### Personality

The Neuroticism, Extraversion, Openness to New Experience-Five Factor Inventory (NEO-FFI) is a questionnaire that contains 60 items on the five personality domains; neuroticism, extraversion, openness to experience, agreeableness and conscientiousness. The item responses are given on a 0 – 5 scale (strongly disagree, disagree, neutral, agree, strongly agree) [65]. A study of Weinstock and Whisman [66] shows that neuroticism is commonly manifested together with depression and anxiety disorders, therefore we only use those 12 items that identify neuroticism. Internal consistency ranges from .68 to .86 [67].

##### Health care utilisation

We use the Trimbos and iMTA questionnaire on Costs associated with Psychiatric illness (TiC-P) [68] to collect data on direct and indirect costs from the patients. The first part of the TiC-P measures the amount of medical care received by the participants, while the second part measures work productivity. We are going to confirm the actual received care, by checking the patients' care status and received care (e.g., medication, number of contacts in primary care and referral policy) during the stepped care project at the general practice settings and the specialized mental health care centers.

##### Health related absenteeism

For the measurement of health related absenteeism, we used the earlier mentioned TiC-P.

##### Costs

We will examine the societal costs which are based on the health care utilisation and health related absenteeism.

##### Satisfaction with care

This is measured via the QUOTE, which stands for Quality Of care Through the patient's Eyes. This questionnaire gives insight in the patient's opinions and believes about the quality of the received care [69]. There are different questionnaires for different diseases. For our study we use the questionnaire for anxiety and depression developed by NIVEL. In the first part of the QUOTE the perceived importance of care-aspects in anxiety and depression are measured. This part contains of 18 items and item-responses are on a 0 – 4 scale (not important – extremely important). The second part of the QUOTE consists of 18 items on the patients experience with the last received care. Item-responses on the second part are on a 0 – 5 scale (yes – no: or no experience).

##### Mastery

We assess the amount of perceived control through the Pearlin Mastery Scale [70]. This scale has 7 items measuring how much an individual perceives having control over things in his or her life. Items are rated on a 4-point scale with higher scores indicating more perceived control. Outcome-scores range from 7 – 35. The questionnaire has good psychometric properties [70] (Table 1).

**Table 1 T1:** Overview of the selected instruments

			**Time of measurement**			
**Aim**	**Measurement**	**Screening**	**Baseline** **(pre-test)** **T0**	**T1**	**T2**	**T3**

						

Demographic variables	Sex	X	X	X	X	X

	Date of birth	X	X	X	X	X

	Native country	X				

	Education		X			

	Income		X			

	Marital status		X			

	Motivation		X (T)			

*Screening*						

Symptoms of depression and anxiety	Extended K10	X	X (T)			

						

*Primary Outcome*						

Symptoms of depression	IDS		X	X	X	X

						

Symptoms of anxiety	HADS-A		X	X	X	X

						

*Secondary Outcome*						

Diagnosis	CIDI		X (T)			X (T)

						

(Dys) Functioning	WSAS		X (T)	X	X	X

						

Quality of life	SF 20		X	X	X	X

						

Symptomatology	4DKL		X			X

						

Alcohol Use	AUDIT		X			

						

Perceived health	EuroQol		X	X	X	X

						

Neuroticism	NEO-FFI		X			

						

Costs of care	TIC-P		X	X	X	X

						

Quality of care	Quote					X

						

Mastery	Pearlin Mastery Scale		X			

						

Suicidal risk	MINI suicide		X (T)			

### Sample Size

A meta-analysis on the effects of psychological treatment on patients with sub-clinical depression shows an effect size of 0.40. Based on a power of 0.80 in a two-tailed test and an alpha of 0.05, we need 100 patients in each condition. Therefore, the total sample size is set at 200.

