### Inclusion and exclusion criteria

We include adults aged 18 – 65 years with one or more of the following DSM-IV diagnoses: major depression (single episode or recurrent), dysthymia, panic disorder (with or without agoraphobia), social phobia or generalized anxiety disorder, including comorbid diagnoses. We also include patients with a minor depression or a minor anxiety disorder. We use the DSM-IV research criteria to define minor depression. The main difference between the criteria of minor and major depression is that for minor depression only two to four out of nine symptoms have to be present, of which at least one has to be a core symptom (depressed mood or markedly diminished interest or pleasure in all, or almost all, activities). As there are no DSM criteria, we define a minor anxiety disorder as a score of 12 or more on the Hospital Anxiety and Depression Scale [31] and dysfunctioning in daily life (household, work and/or social relations). Exclusion criteria are psychotic or bipolar disorder, current (< 2 months) treatment (medical/psychotherapy) for psychological problems, prominent suicide ideation, severe alcohol problems (> 20 on the Alcohol Use Disorders Identification Test (AUDIT)[32], no motivation for treatment and insufficient knowledge of the Dutch language.

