### Statistical Analysis

All analyses will be conducted according to the intention-to-treat principle. All respondents who have been randomised will be included in the analyses examining the effects of the intervention. Missing data will be imputed using regression imputation. The effectiveness of the stepped care program is measured via the primary outcomes: the HADS (anxiety) and IDS (depression). It is useful to know not only wether the effectiveness is statistically significant, We will use Cohens' *d *[71] to measure the size of the effect. Furthermore, GEE-analysis will be used to examine differences in speed of recovery between the two groups [72]. Additionally, we will report the percentage of patients who have recovered at the moment of the last assessment. In order to do so we will calculate the relative risk.

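### The 200 patients enrolled equal the number needed with complete outcome data, so the stated power of 0.80 holds only with essentially no loss to follow-up

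*Protocol article*

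**What the plan says.** The Sample Size section of the protocol article gives the whole derivation. The effect size is borrowed: "A meta-analysis on the effects of psychological treatment on patients with sub-clinical depression shows an effect size of 0.40". The calculation follows: "Based on a power of 0.80 in a two-tailed test", with alpha 0.05. The enrolment total is then drawn from it directly: "we need 100 patients in each condition. Therefore, the total sample size is set at 200". No attrition rate or inflation factor appears there or elsewhere in the article.

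The Statistical Analysis section commits to including all randomised patients and adds: "Missing data will be imputed using regression imputation". It names HADS (anxiety) and IDS (depression) as the primary outcomes. Table 1 shows both measured at baseline (T0) and at T1, T2 and T3, that is, at 8, 16 and 24 weeks.

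The inclusion criteria list major depression, dysthymia, panic disorder, "social phobia or generalized anxiety disorder, including comorbid diagnoses", and also admit minor depression and minor anxiety disorder.

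**The concern.** A power formula returns the number of patients who contribute outcome data. Here that number became the number to randomise, in a trial that relies on repeated self-report questionnaires and plans for missing values. Any loss then takes the design below its stated power. A null result would be read against 80% power when the chance of detecting 0.40 could have been noticeably lower.

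The effect size adds a second uncertainty. It describes psychological treatment of sub-clinical depression. Minor depression in this trial plausibly overlaps with that population. Major depression, dysthymia and the anxiety disorders do not, and the article gives no reason for carrying 0.40 over to them or to an anxiety scale.

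**Working it through.** **Inputs from the Sample Size section:** d = 0.40 (standardised, so SD = 1), two-sided alpha 0.05, power 0.80, 100 per arm, 200 in total.

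**Assumed, because the article gives no figure:** loss of 10, 20 or 30%, equal in both arms, with each lost patient contributing nothing; baseline–outcome correlation r = 0.5; sensitivity effect d = 0.30.

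**Step 1, reproduce the plan's figure.** Normal approximation: n per arm = 2(1.960 + 0.842)²/0.40² = 2 × 7.849/0.16 = 98.1, so 99. The two-sample t-test solution is 99.08, so 100. The stated 100 is confirmed.

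**Step 2, how much slack there is.** By t-test, power is 0.804 at 100 per arm and 0.7997 at 99. One lost patient per arm takes the design just under 0.80.

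**Step 3, power under loss.** Analysable n per arm = 100 × (1 − loss). Power is approximately Φ(d√(n/2) − 1.960). For n = 80: 0.40 × √40 = 2.530, and Φ(0.570) = 0.716; the t-test gives 0.710. The detectable effect is the d at which power is 0.80 for that n. For the baseline-adjusted analysis, d is replaced by d/√(1 − r²) = 0.40/√0.75 = 0.462. The table gives t-test values.

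| Assumed loss | n per arm | Power, d = 0.40, unadjusted | Detectable d at power 0.80, unadjusted | Power, d = 0.40, baseline-adjusted, r = 0.5 |
|---|---|---|---|---|
| 10% | 90 | 0.76 | 0.42 | 0.87 |
| 20% | 80 | 0.71 | 0.45 | 0.83 |
| 30% | 70 | 0.65 | 0.48 | 0.77 |

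Intermediate losses of 15% and 25% give unadjusted power of 0.74 and 0.68.

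**Step 4, sensitivity to the borrowed effect.** With 100 per arm and no loss, d = 0.30 gives power 0.56.

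**Step 5, for scale.** Keeping 100 analysable per arm would require randomising 100/(1 − loss): 112 per arm (224 in total) at 10%, 125 (250) at 20% and 143 (286) at 30%.

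**The case against.** The strongest case on the other side is that nothing has been miscalculated and that the size of the shortfall depends on inputs the article does not give. Most of that stands.

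- **The calculation is correct.** A reader might infer an arithmetic error. There is none; the fault lies in how the result is used.
- **The loss rate is unknown.** A reader might infer that the real chance of detecting 0.40 was about two in three. That is true only for an unadjusted analysis at roughly 25–30% loss. At 10% it is about three in four.
- **The figures are a worst case for each loss rate.** Imputing a missing week-24 score from earlier IDS or HADS scores can recover part of the information. It cannot recover all of it, so including every randomised patient does not by itself restore 0.80.
- **The primary comparison may turn out to be baseline-adjusted.** The article does not say that it is unadjusted, and such detail is often left to a fuller document. But the Sample Size section claims no gain from adjustment.
- **HADS is not without any sizing basis.** The calculation uses a standardised effect, so 100 per arm gives the same power for d = 0.40 on any continuous scale. What is missing is a reason to expect 0.40 on an anxiety measure.
- **Two primary outcomes might suggest power at alpha 0.025 each.** The plan states 0.05 and no split, so such a figure would not describe this trial.
- **The source of 0.40 is disclosed.** A reader might infer that the true effect must be smaller. The documents do not show its direction. At d = 0.45, power with 20% loss would be about 0.81.

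One could add that a journal article condenses the full protocol, so an allowance might be stated there. But the printed figures leave no room for one: 99.08 rounds to 100, and 2 × 100 is the total.

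**Conclusion.** The point holds as a matter of design assumptions. The stated 0.80 describes a trial with essentially complete outcome data, and the plan itself expects missing data. The shortfall is moderate and conditional: relative to 0.80, about 4 percentage points at 10% loss, 9 at 20% and 15 at 30%. This rests on an unadjusted comparison, a true effect of 0.40, equal loss in both arms and no information recovered from lost patients. Baseline adjustment with r = 0.5 would bring power above 0.80 at 10% and 20% loss and to 0.77 at 30%.

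The effect-size point is narrower. The value 0.40 comes from a population that only partly overlaps with the one enrolled, and its use for anxiety is not justified. Because the documents do not say whether the true effect is larger or smaller, 0.30 is a sensitivity case and not a prediction.

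**What to change.** Keep 200 patients and change the statement:

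1. Say that 100 per arm is the number with outcome data needed for d = 0.40, and give power or detectable effect over an assumed 10–30% loss: unadjusted power 0.76 to 0.65, detectable effect about 0.42 to 0.48.
2. Specify a baseline-adjusted comparison for IDS and HADS, both already measured at T0. State its power as conditional on an assumed correlation; at r = 0.5 it is about 0.87, 0.83 and 0.77 at 10, 20 and 30% loss.
3. Say that 0.40 is taken from sub-clinical depression, that this only partly matches the enrolled population, and that its use for anxiety is an assumption. Show d = 0.30 (power 0.56 with no loss) beside it.

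The cost is a few sentences and a commitment to baseline adjustment. It needs no extra patients or measurements. The unadjusted power will read less favourably than the single figure of 0.80.

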### Statistical Analysis

All analyses will be conducted according to the intention-to-treat principle. All respondents who have been randomised will be included in the analyses examining the effects of the intervention. Missing data will be imputed using regression imputation. The effectiveness of the stepped care program is measured via the primary outcomes: the HADS (anxiety) and IDS (depression). It is useful to know not only wether the effectiveness is statistically significant, We will use Cohens' *d *[71] to measure the size of the effect. Furthermore, GEE-analysis will be used to examine differences in speed of recovery between the two groups [72]. Additionally, we will report the percentage of patients who have recovered at the moment of the last assessment. In order to do so we will calculate the relative risk.

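### Regression imputation, as the only stated missing-data method, ignores imputation uncertainty and misclassifies recovery; depending on unstated predictors it either breaks the 5% level and inflates Cohen's d or dilutes d

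*Protocol article*

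**What the plan says.** The Statistical Analysis section gives one rule for incomplete data: "Missing data will be imputed using regression imputation". It also fixes the analysis set: "All respondents who have been randomised will be included in the analyses examining the effects of the intervention". The completed data therefore feed the comparisons of IDS and HADS, the Cohen's d that is used "to measure the size of the effect", the GEE analysis of speed of recovery, and a relative risk, for which "we will report the percentage of patients who have recovered at the moment of the last assessment".

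The section on assessments and the definition of recovery makes recovery a composite: "Recovery is defined as a score below the cut-off score on all three of the following questionnaires". The cut-offs are IDS below 14, HADS below 8 and WSAS below 6.

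The article does not say whether the imputation is single or multiple, whether a residual is drawn, or which predictors are used (treatment arm included). It gives no expected missing-data rate.

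**The concern.** A predicted value is not an observation. If it replaces the missing score and the analysis proceeds on 200 apparently complete records, three things go wrong.

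- The standard error is computed as if nobody had dropped out, and the imputed values lie on the regression line without scatter. The reported error is then too small.
- The SD of the completed data shrinks. Cohen's d divides by an SD, so it moves as well.
- Recovery is a threshold on three scores. Predicted values cluster around the conditional mean, so the share of dropouts below the cut-offs is not the share that would truly have recovered.

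Both primary outcomes, the effect size and the relative risk depend on this sentence. The method is stated, not left open, so an analysis plan that followed it would inherit the problem.

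**Working it through.** **The plan's own figure.** The Sample Size section starts from a meta-analysis that "shows an effect size of 0.40", and continues: "Based on a power of 0.80 in a two-tailed test and an alpha of 0.05". The normal formula gives n = 2(1.960 + 0.842)²/0.40² = 98.1, so 99 per arm. The t-based value is 99.1, so 100. Power at 100 per arm is 0.807. The figure reproduces, and the present point does not affect it.

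**Assumed inputs.** Missing proportion m = 10%, 20% or 30%, completely at random; baseline-outcome correlation ρ = 0.5; outcome SD 1; imputation from the baseline score, with or without arm; two-sample comparison and Cohen's d on the completed data at one assessment. The article gives neither m nor ρ.

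**Predicted value, arm in the model.**
- SD of completed data: √(1 − m(1 − ρ²)). At m = 20%: √0.85 = 0.922.
- Reported SE: 0.922 × √(2/100) = 0.130.
- Actual SE: √{(2/100)[ρ² + (1 − ρ²)/(1 − m)]} = √(0.02 × 1.1875) = 0.154 (simulated 0.155).
- Type I error: 2Φ(−1.96 × 0.1304/0.1541) = 2Φ(−1.66) = 0.097.
- Cohen's d for a true 0.40: 0.40/0.922 = 0.434.

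| Missing | Type I, formula | Type I, simulated | Coverage, no effect | d, formula | d, simulated |
|---|---|---|---|---|---|
| 10% | 0.070 | 0.072 | 0.928 | 0.416 | 0.42 |
| 20% | 0.097 | 0.098 to 0.100 | 0.900 | 0.434 | 0.44 |
| 30% | 0.133 | 0.129 to 0.131 | 0.869 | 0.454 | 0.46 |

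Simulated type I error at ρ = 0.3 and 0.7 is 0.113 and 0.082 at 20% missing, and 0.165 and 0.102 at 30%.

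**Residual draw added, arm in the model.** The bias in d disappears (0.40 to 0.41), but type I error is still 0.069 to 0.118 over 10% to 30% missing.

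**Predicted value, arm omitted.** Imputed patients carry no treatment difference, so d is about 0.40(1 − m)/√(1 − m(1 − ρ²)). This gives 0.374, 0.347 and 0.318; simulation gives 0.37 to 0.38, 0.35 and 0.32. Type I error is 0.046 to 0.052. Coverage at a true d of 0.40 is close to nominal at 10% missing, about 0.90 to 0.91 at 20% and about 0.83 to 0.84 at 30%.

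**Recovery, simplified to one scale** (no effect, ρ = 0.5). For a cut-off c SD from the mean, the share of dropouts imputed as recovered is Φ(c/ρ), against a true Φ(c).
- c = −0.7: Φ(−1.4) = 8% against 24%; about 23% of dropouts are misclassified.
- c = 0: 50% against 50%.
- c = +0.3: Φ(0.6) = 73% against 62%, the opposite direction.

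Relative risk at c = −0.7, d = 0.40, 20% missing (true 0.382/0.242 = 1.58):
- Arm in the model: (0.8 × 0.382 + 0.2 × 0.274)/(0.8 × 0.242 + 0.2 × 0.081) = 0.361/0.210 = 1.72.
- Arm omitted, both arms imputed at Φ(−1.0) = 0.159: (0.8 × 0.382 + 0.2 × 0.159)/(0.8 × 0.242 + 0.2 × 0.159) = 0.337/0.225 = 1.50.

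**Recovery on all three scales** (20% missing; assumed cross-scale correlation 0.6, baseline-outcome correlation 0.4 or 0.6). With no effect, 1% to 3% of dropouts are imputed as recovered against a true 9% when the cut-offs lie 0.7 SD below the control mean, and 8% to 13% against 18% at 0.3 SD below. With cut-offs at the mean the rate matches under no effect, but at d = 0.40 it is too high (42% to 48% against 36%). At d = 0.40, true relative risks of about 1.58, 1.78 and 2.10 become 1.67 to 1.76, 1.91 to 2.07 and 2.27 with arm in the model, and 1.40 to 1.43, 1.59 to 1.60 and 1.91 to 1.99 with arm omitted.

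**Replacement.** Multiple imputation (20 imputations, arm in the model, Rubin's rules, ρ = 0.5, 10% to 40% missing) gives type I error 0.048 to 0.055, coverage 0.943 to 0.959 and mean d 0.40 to 0.405. In the one-scale setting, the recovery rate among dropouts under no effect equals the true 24%.

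The GEE analysis was not simulated. It would use the same completed data.

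**The case against.** A reader might infer that the sentence always inflates d, always loses the 5% level and leaves hardly any dropouts counted as recovered. The document does not support that. It does not list the predictors: with arm omitted, the 5% level is kept and d is diluted. It does not exclude a residual draw: with one, d and the group recovery rates are unbiased. It gives no expected recovery rate: with cut-offs at or above the mean, the share of dropouts imputed as recovered is right or too high. These objections stand, and each consequence has to be stated with its condition.

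It is also fair that single imputation is the ordinary meaning of the term, not something the text says, and that a condensed article may leave predictors and the number of imputations to a fuller document. That covers detail within a sound method. It does not cover naming a method that fails in every single-imputation version examined; if multiple imputation was meant, the sentence still needs to say so.

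On size, imputing from baseline alone may overstate the harm. With monotone dropout and T1 and T2 scores used where present, type I error was about 0.07, 0.09 and 0.11 at 10%, 20% and 30% missing: smaller, but not nominal.

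**Conclusion.** The concern holds in conditional form. Read in its ordinary sense, the stated rule ignores imputation uncertainty and misclassifies recovery among dropouts. With arm in the imputation model, type I error is about 7%, 10% and 13% and coverage about 93%, 90% and 87% at 10%, 20% and 30% missing, and d is about 5% to 15% too large. A residual draw cures the bias in d but not the excess type I error. With arm omitted, the test level holds, but d falls to about 0.38, 0.35 and 0.32 against 0.40, and interval coverage at a true effect fails from 20% missing. Recovery percentages and the relative risk are biased in a direction set by where the three cut-offs lie relative to the T3 mean and by whether arm is a predictor.

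The sizes rest on an assumed missing rate, an assumed correlation of 0.5 and data missing completely at random. At 10% missing the harm is modest.

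**What to change.** Replace the imputation sentence with one of two options.

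- Multiple imputation for all outcome analyses, with arm and all available T0 to T3 IDS, HADS-A and WSAS scores as predictors, pooled by Rubin's rules. Recovery status is derived from the three imputed scores within each data set before pooling.
- A likelihood-based mixed model on the observed IDS and HADS-A scores, with multiple imputation as above for recovery and its relative risk.

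The cost is one paragraph, a little more analysis work and slightly wider confidence intervals. Under the multiple imputation simulated here (ρ = 0.5), power for d = 0.40 is 0.77, 0.72 and 0.69 at 10%, 20% and 30% missing, against 0.807 with complete data. Missing data cause that loss; treating predicted values as observed only hides it.
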